### Study Hypothesis, Objectives, and Rationale

#### Hypothesis

Improved competencies of family caregivers may reduce their stress and burden and promote the well-being of older adults as well as increase caregivers’ productivity. Functional training exercises for older people will preserve active aging whereas better home care will prevent LTC needs and hospitalization and could decrease health care costs. We hypothesized that there will be differences between the intervention clusters utilizing CIIC services and control clusters in terms of family caregiver burden, functional ability of the older persons, and their QOL.

Such an intervention will be evaluated in a randomized controlled trial, but individual randomization is not realistic and threatens the validity of the results by contamination. Therefore, a clustered randomized controlled design will recruit eligible villages and consented community residents, older persons, within the village as a cluster.

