#### Objectives

This study aims to assess the effectiveness of a CIIC facility and its functions to assist families providing LTC for older adults in terms of reducing caregivers’ burden as the primary outcome. Another objective is to evaluate the effectiveness of the CIIC model in terms of the following secondary outcomes: impact on ADL, depression, and QOL of older people.

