#### Secondary Outcomes

Secondary outcomes consist of biopsychosocial indicators including ADL, depression, and QOL of older people, which will be compared between intervention and control groups.

Functional ability will be assessed by applying the Barthel Index for ADL assessment [16], which measures the level of ability for 10 basic items (bowel movement, incontinence, grooming, toileting, feeding, transfer, mobility, dressing, stairs, bathing). Total possible scores range from 0 to 20, with lower scores indicating increased disability.

Depression will be screened by applying the Geriatric Depression Scale (GDS), which is internationally commonly used, validated, and regularly used in Thailand [17].

Health-related QOL will be measured with the EQ-5D-5L questionnaire [18] using the EQ visual analogue scale (EQ VAS) [18,19]. A validated Thai version of the instrument is already available and will be used after piloting. The EQ-5D-5L measures 5 dimensions with 5 levels: mobility, self-care, usual activities, pain/discomfort, and anxiety. The EQ VAS is a measure of overall self-rated health status with a vertical VAS where the end points are labeled “Best imaginable health state” and “Worst imaginable health state.”

Cost for the intervention will be calculated in terms of intervention cost, family cost, and community cost. The details of the intervention cost will inform the estimated cost when expanding the area covered by the CIIC services.

The first possible outcome of the implementation of the CIIC intervention is promoting the capacity of the family caregivers through technical training, early detection of dependency problems, and respite care when the caregiver is overburdened in addition to linking families and primary health care services. The intervention components such as the (1) community respite home and (2) technical capacity building of the caregiver are directly targeting the reduction of caregiver burden.

Therefore, we set caregiver burden as the primary outcome of the study. ADL is also an important outcome of the component. Although we set these as the primary and secondary outcomes, respectively, in terms of the research methodology, they are both important outcomes of the study.

Selecting an outcome that is directly related to most of the intervention practically, we chose caregiver burden as the primary outcome. In a country with an FLTC system as its backbone, this outcome is more practical.

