### Statistical Methods

The analysis will follow the intention-to-treat analysis approach. Outcomes will be compared between intervention and control clusters after 6 months of intervention.

To assess the effectiveness of the intervention, the primary outcome, CBI, will be compared between intervention and control arms after 6 months of intervention. Depending on the nature of the variables, *t* tests, chi-square tests of cluster summary measures, or multivariate analyses will be applied. Data distribution and homogeneity will be checked and ensure the assumption of statistical tests. Cluster-level summary statistics will be compared. A random effects model will be applied to control possible confounders in individual and cluster levels.

The intervention in the CIIC trial is a complex intervention with several components of prevention, training, and service. It is basically empowerment of the community. Therefore, a village as a random effect is due to population and social economic status, and participation of the community is considered as source of variation.

To evaluate the impact of the intervention on the secondary outcomes (ADL for dependency, GDS for depression, and EQ-5D-5L for QOL), the analyses will compare the 2 arms by applying a multivariate analysis of variance model.

Afterwards, the cost of the intervention will be analyzed in terms of both the primary outcome and secondary outcomes. Statistical significance is defined as *P*<.05 with 95% confidence intervals.

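### The only method named for the secondary outcomes is a joint MANOVA, whose test shows neither which of ADL, depression or QOL changed nor in which direction; the protocol commits to no per-outcome contrast

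*Protocol article*

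**What the plan says.** In the protocol article, Statistical Methods gives the secondary outcomes (ADL, GDS and EQ-5D-5L) a paragraph of their own with one method: "the analyses will compare the 2 arms by applying a multivariate analysis of variance model". The t tests, the chi-square tests of cluster summaries and the random effects model appear earlier, in the paragraph on the Caregiver Burden Inventory. A closing sentence for the whole section, beginning "Statistical significance is defined as", sets P<.05 with 95% confidence intervals. It does not say which quantities the intervals are for.

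The questions are posed by outcome. Objectives lists "secondary outcomes: impact on ADL, depression, and QOL of older people". Hypothesis expects differences between arms "in terms of family caregiver burden, functional ability of the older persons, and their QOL". Secondary Outcomes adds that "ADL is also an important outcome of the component" and ranks it beside caregiver burden in importance.

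**The concern.** A joint test of three means answers one question: do the arms differ anywhere in the three-outcome profile? The stated questions are whether the care model improves function, depression and quality of life. A significant joint P value could come from a gain in ADL with a loss on depression, and could still be reported as an impact of the model. It could equally come from harm on all three.

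If per-outcome contrasts are chosen only after the joint result is known, the choice of which to report, and whether to adjust, is made with the data in view. Three independent unadjusted tests at .05 carry a family-wise error of 1 - 0.95³ = 14.3%.

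**Working it through.** The article gives no figure for the power or size of the MANOVA, so there is no stated number to reproduce. The check has four steps.

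**1. What the joint test can show.** With two arms of n each, T² = (n/2) d′S⁻¹d, where d is the vector of three mean differences and S the pooled covariance matrix. Replacing d by -d leaves T² unchanged, so benefit on all three outcomes and equal harm on all three give the same P value. It is also a single number, so it identifies no outcome. This holds at any correlation and however villages are handled.

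**2. Consistent versus mixed effects.** Inputs, all assumptions:
- Every score is coded so that higher is better. The Barthel Index already runs that way ("Total possible scores range from 0 to 20, with lower scores indicating increased disability"). The article does not state the direction of the GDS; I take it as reversed where needed.
- The three standardised shifts are equal in size.
- The scores share a common correlation ρ.
- The noncentrality of each outcome alone is 7.849/3 = 2.616, which is 37% power on 1 df at two-sided .05.

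The joint noncentrality is 2.616 × v′R⁻¹v, where v holds the signs of the shifts:
- all three improve: v′R⁻¹v = 3/(1+2ρ)
- two improve, one worsens: v′R⁻¹v = (3+5ρ)/[(1+2ρ)(1-ρ)]

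At ρ = 0.4 these are 3/1.8 = 1.67 and 5/1.08 = 4.63, a ratio of 2.8. Power is from the noncentral chi-square on 3 df:

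| ρ | v′R⁻¹v, consistent | v′R⁻¹v, mixed | Power, consistent | Power, mixed |
|---|---|---|---|---|
| -0.2 | 5.00 | 2.78 | 87% | 61% |
| 0 | 3.00 | 3.00 | 64% | 64% |
| 0.2 | 2.14 | 3.57 | 49% | 73% |
| 0.4 | 1.67 | 4.63 | 39% | 84% |

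**3. Does it survive few clusters?** With 6 village summaries per arm (noncentral F on 3 and 8 df), an assumed shift of 1.5 between-cluster SD and ρ = 0.5, power is 54% for consistent and 98% for mixed effects. The pattern is the same.

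**4. Would separate tests have more power?** Let one outcome move, with noncentrality 7.849 (80% power unadjusted):
- Joint test: noncentrality 7.849 × (1+ρ)/[(1+2ρ)(1-ρ)]. At ρ = 0 this is 7.849, power 64%. At ρ = 0.4 it is 7.849 × 1.296 = 10.17, power 77%.
- Holm over three P values, by simulation: about 66% for that outcome at either correlation.

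When all three improve at ρ = 0.4 with the step 2 shifts, Holm gives 25% per outcome and 44% for at least one, against 39% for the joint test. Separate tests therefore bring no general power advantage.

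**The case against.** The strongest reply is that the article names a MANOVA model, not an omnibus P value alone. A fitted two-arm MANOVA yields a mean difference for each outcome, and the promise of 95% confidence intervals makes most sense if those differences are to be reported. Follow-up contrasts are also commonly left to an analysis plan, and none is shown here. This stands against one stronger reading: a reader might infer that the secondary objectives get no estimate at all, and the article does not say that. What remains is that the one method it fixes is aimed at a different question from its objectives, and it ties neither contrasts nor intervals to individual outcomes.

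Three other stronger readings also fail:
- **The joint test always favours mixed effects.** This needs positive correlation between benefit-oriented scores. That is plausible, since EQ-5D-5L includes mobility, self-care and anxiety, but no value is given. The contrast vanishes at zero correlation and reverses at -0.2.
- **The joint test wastes power.** A fall from 80% to 64% when one uncorrelated outcome moves compares it with an unadjusted test. Holm falls to about 66%, and at correlation 0.4 the joint test does better (77%).
- **A joint analysis loses many more people.** With 10% missing independently on each score, requiring all three would drop 1 - 0.9³ = 27%. But the scores come from interviewer-administered questionnaires at the same follow-up, so they may well be missing together. With full overlap the loss is 10%, the same as for separate models.

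**Conclusion.** The point holds in a limited form. The only method named for the secondary outcomes has a joint test that identifies neither the outcome nor the direction, while the objectives ask about "impact on ADL, depression, and QOL of older people". That conclusion needs no numerical assumption.

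The greater sensitivity to mixed effects is conditional. It rests on positive correlation, equal shifts and about 37% power per outcome. Over correlations from 0 to 0.4, the power gap in favour of the mixed pattern grows from nil to 45 percentage points (84% - 39%).

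The matter affects interpretation of the secondary outcomes only. The primary comparison of caregiver burden is untouched. It is worth correcting because the correction is nearly free.

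**What to change.** Replace the MANOVA sentence with one model per outcome: Barthel Index, GDS and EQ-5D-5L. Each should include village as a random effect, or be based on village summaries, with small-sample degrees of freedom suited to 12 clusters. Without the village term the intervals would not be valid. Each model should use everyone with that outcome and report the between-arm difference at 6 months with its 95% confidence interval. Apply Holm's correction across the three P values if they are used for claims. Keep the MANOVA, if wanted, as a supporting test only.

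This changes wording and needs no new data or participants. The cost is in power under Holm: a single outcome with 80% power unadjusted has about 66%. That is close to the joint test with uncorrelated outcomes (64%) and below it at correlation 0.4 (77%). The gain is an answer for each stated objective, with its direction and size.

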## Results

The CIIC facility has been established and equipped to provide care services to older persons who requested and were eligible to receive the service. Community-based care prevention programs have been launched in the intervention clusters. Nurses from the CIIC visited the houses of older persons upon the family caregiver’s request for care planning advice. Family caregivers received training and assistance. However, the COVID-19 pandemic delayed the interventions (Figure 3).

Care prevention exercises have been launched in the communities of the 6 intervention clusters. The adoption rate was 100%. Community stakeholders, municipality authorities, and the Ministry of Public Health of Thailand actively collaborated with the research team. The community empowerment approach consisted of training volunteers to be trainers of the exercise groups, providing group exercise DVDs and televisions to use in the group exercise to each cluster, providing home exercise DVDs and posters for maintaining exercise at home, a calendar to record exercise frequency, and a line group for communication among the participants. Community-based, functional-training, group exercise activities were launched in February 2020. The research project provided DVDs free of charge to the intervention arm participants. During the suspension of the community-based activities due to the COVID-19 pandemic, care prevention exercises were sustained by applying home exercise.

The COVID-19 pandemic and declaration of emergency postponed the intervention program until June 2020. Afterward, the program was resumed. The study was implemented until December 2020. Since then, the CIIC trial is undergoing evaluation. The evaluation will be completed by the end of March 2021. The timeline for study implementation could be extended by the local ethical committee and WHO Ethical Review Committee.

## Discussion

### Principal Findings

Health and social care that is accessible in a universally covered scheme is an expectation of all second wave-aging countries like Thailand. They need an aging care model that can enhance FLTC and link to primary health care services, while being integrated into the community and local government in each municipality. CIIC is expected to provide a potential model that can link families and communities to local formal services and funding. In addition, it will promote active aging through a community-based care prevention exercise program for older persons.

The CIIC facility and services will introduce formal intermediary care services to the Thai community whereby informal care will be strengthened through helping families to improve their capacity for the care of older people [7]. Locating CIIC services in a neighborhood environment is designed to raise local attention and people’s awareness, familiarity, and trust within the social network of the local community [21]. This is a strategy to realize the integration of older people into community care services.

Furthermore, we introduced 3 steps as part of a prevention strategy in the CIIC services (Figure 4). The first step is a community LTC prevention exercise program co-created to function as community empowerment. Participation in such community exercises can promote autonomy and active aging, with the potential outcome that will prevent dependency and need for LTC [22]. Second, when there is little care need, the older person can enjoy staying at home with their families, thereby improving their chances of “aging in place” [4]. When family caregivers face burnout, older persons will be able to access a formal care service in the community. Overall, families will be assisted through training, direct help, and a respite service provided by the CIIC [9]. Again, the hope is that it can prevent unnecessary LTC costs. Third, when older people remain active and healthy, health care needs may be reduced, thereby avoiding unnecessary hospital admission and saving health care costs. Screening of ADL and for common noncommunicable diseases will identify unmet needs earlier and prevent age-related morbidity and disability. Therefore, in the long-term, the interaction between the CIIC and primary health care services could be harmonized, leading to better integration and could be a step to realizing universal access to long-term and health care in Thailand.

**Figure 4 figure4:**
[figure not shown]
Components of the intervention in the 2 arms of the Community-Integrated Intermediary Care (CIIC) trial.

#### Dissemination of Results and Publication Plan

A lay summary of the results will be communicated back to the communities via community radio and relevant social media outlets. The results will be reported back to the WHO Kobe Centre, published in international peer-reviewed journals, and relayed to the Ministry of Health of Thailand, local authorities, and development partners in aging and LTC services in the Asia-Pacific region.

#### Future Implications

With the CIIC model, the strategy for sustainability could be realized through mobilizing community participation and assets towards the shared value of active aging and sustainable social care for the older person. Therefore, we expect that the model of intermediary care in this study will yield a sustainable, affordable, and universally accessible model that could enhance FLTC in Thailand and other similar rapidly aging countries in Asia.

#### Challenges and Limitations

Cluster randomization may increase the risk of imbalance in the 2 arms at baseline. This approach of randomization we practiced in CIIC may have limitations but would minimize the residual confounders caused by differences in characteristics of the municipalities. However, this is the best pragmatic approach for the current trial. The results of randomization should be checked carefully at baseline by comparing the aggregate-level summary.

We do not have data about the desirability of temporary, short residential stays at the CIIC facility for older adults and their families. We may have underestimated the demand and therefore, also the required resources. Researchers have consulted with local governments about the possibility of tapping into reserve capacity and resources. Social distancing measures in the COVID-19 pandemic delayed the activities, but we adhered to those measures to ensure the safety of participants.

#### Conclusion

With a rapidly aging population, sustainable health and social care provided to older people in their community are urgently required. We see this as a potential step to the realization of universal health coverage and well-established primary health care services that are inclusive of aging populations in Thailand. The evidence and lessons learnt in this study are expected to be beneficial to other similar countries in Asia.

## Abbreviations

ADL: activities of daily living
ASEAN: Association of Southeast Asian Nations
CBI: Caregiver Burden Inventory
CIIC: Community integrated intermediary care
EQ-5D-5L: EuroQol 5-dimensions 5-levels
FLTC: family-based, long-term care
GDS: Geriatric Depression Scale
LTC: long-term care
QOL: quality of life
VAS: visual analogue scale
WHO: World Health Organization
